### Recruitment {15}

Patients with fractures of the distal tibia will be recruited at up to 20 German study sites.

## Assignment of interventions: allocation

### Sequence generation {16a}

Treatment allocation to coated or uncoated investigational device will be randomized in 1:1 ratio. With a stratification by site and by severity of the soft tissue lesion [3 groups: (1) closed and Gustilo-Anderson type I open; (2) Gustilo-Anderson type II open; (3) Gustilo-Anderson type III open] [13, 14]^.^

### Concealment mechanism {16b}

Randomization is performed via the eCRF by the unblinded surgeon on the day of the implantation. Blinded study team members or the sponsor cannot see the patient's treatment allocation of the patient in the eCRF.

### Implementation {16c}

On the day of implantation, the surgeon will use the randomization functionalization of the eCRF for treatment allocation.

## Assignment of interventions: Blinding

### Who will be blinded {17a}

The implanting surgeon and staff involved in the surgery or handling of the investigational device will be unblinded to treatment allocation because the difference between coated and uncoated implants is visible by eye. The subject will be blinded to treatment allocation. The blinded evaluator (medical assessor) will be blinded to treatment allocation and responsible for treatment decisions and assessment of key study endpoints. Sponsor, study management, and statistical teams in addition to adjudication board and central laboratory will also be blinded.

### Procedure for unblinding if needed {17b}

If unblinding is necessary, the investigator can unblind a patient’s treatment allocation in the eCRF. Before unblinding, the investigator has to give the reason for unblinding on an extra page on the eCRF and is informed that unblinding should only happen if definitely necessary according to the opinion of the investigator.

## Data collection and management

### Plans for assessment and collection of outcomes {18a}

On site, data will be derived from patient records and collected with an electronic Case Report Form (eCRF) which is Good Clinical Practice (GCP) Compliant. At the study visits, patients will be examined by an investigator and questionnaires will be answered. Blood samples for safety data will be performed at the local laboratories, whereas blood and wound fluid samples for silver analysis will be performed at a central laboratory at the end of the study. The radiographic data and photographs of the soft tissue acquired during the study will be uploaded to the eCRF.

### Plans to promote participant retention and complete follow-up {18b}

The patients will be informed extensively about the study set-up and the requirements during the recruitment phase. It will be stressed that participation in all follow-up visits is important for the success of the clinical trial. Nevertheless, patients are allowed to withdraw from the study at any time without any reason or explanation. Patients will be asked to do at least a close-out visit after withdrawing their consent.

Patients who deviate from the clinical investigational plan will be followed up as all the other patients to ensure their safety.

### Data management {19}

Patient data, answered questionnaires, radiographic data, and photographs of the soft tissue will be collected with an eCRF. Informed consent forms will be stored within the hospitals in a locked room. All (S)AEs and protocol deviations will be documented and reported via the eCRF. The eCRF has an audit trail system to document all changes made to the data. Source data will remain at the study sites. All research data will be archived for at least 15 years after the end of the clinical trial.

### Confidentiality {27}

After signing the informed consent form, the subject will receive a study identification code. The identification code list will only be available to the study team at site and stored in the ISF. All data entered in the eCRF will only be associated with the study identification code. Radiographic images will be blackened if necessary. Only anonymized data will be reported in publications.

### Plans for collection, laboratory evaluation, and storage of biological specimens for genetic or molecular analysis in this trial/future use {33}

Not applicable, no leftover material will be stored.

## Statistical methods

### Statistical methods for primary and secondary outcomes {20a}

All statistical calculations will be made in SAS. A statistical analysis plan will be developed and finalized before data base lock and unmasking describing in detail the planned statistical analysis.

All study endpoints of this study will be summarized using descriptive summary statistics, i.e., arithmetic mean, standard deviation, minimum, median, and maximum for quantitative variables by treatment group. For qualitative variables, absolute and relative frequencies will be reported. For event-based variables (e.g., AEs) the number of events as well as the incidences (i.e., number and percentage of affected subjects) will be provided.

The primary null hypothesis that will be tested is that the difference in proportion of subjects who have at least one predefined AADE (between investigational coated device and comparator (uncoated)) is greater than or equal to 0.1 (i.e., the alternative hypothesis is successfully met if the upper bound of a two-sided 90% CI is less than +0.1).

### Interim analyses {21b}

No interim analysis for this clinical trial is planned.

### Methods for additional analyses (e.g., subgroup analyses) {20b}

No subgroup or other additional analyses for this clinical trial is planned.

### Methods in analysis to handle protocol non-adherence and any statistical methods to handle missing data {20c}

The study will employ four analysis sets. (1) Surgical Failures: a randomized subject is assigned to the set of surgical failures if the device could not be successfully implanted. (2) Full Analysis Set employs the intent-to-treat principle and includes all subjects randomized. The Full Analysis Set population is used for all intent-to-treat-based analyses. Subjects are analyzed as they were randomized. (3) Safety Analysis Set includes all treated subjects in the Full Analysis Set who are not Surgical Failures. The Safety Analysis Set is used for all primary and secondary analyses and will be analyzed as implanted. (4) The Per Protocol set will include all subjects in the Full Analysis Set without any major protocol violations. Deviations, which are occurring due to a safety issue (e.g., drop-out due to AE) will not be excluded from the Per Protocol set. Key analyses will be performed using the Per Protocol population if the number of per protocol patients is less than 90% of the full analysis set.

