### Criteria for discontinuing or modifying allocated interventions {11b}

At any time and without any reason, patients can withdraw from the clinical trial without consequences. Because of compliance reasons, the investigator can end the patient’s participation. The collected data of patients who did not end the trial per protocol will be part of the Safety Analysis Set.

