### Outcomes {12}

Since this clinical trial should demonstrate the non-inferiority of the silver-coated implants the primary outcome is the comparison of predefined AADEs of patients treated with the investigational product and patients who received the comparator. A list of AADEs was defined based on experiences with the non-coated implants (see Table 1). Other outcomes of interest are:To investigate the proportion of subjects with device-related infections occurring after successful implantation of the study device and end of the 12-month FU and compare the rate between the treatment arms.To investigate fracture healing assessed by local and central reviewer and compare the rate of completely healed subjects between treatment arms.To investigate the number of hospitalizations occurring in the first 12 months post-implantation and the nights spent in hospital and compare the numbers between treatment arms.To investigate the change in American Orthopaedic Foot and Ankle Score (AOFAS) at each FU visit and compare endpoint between the treatment arms.To investigate the change in average pain at rest at each FU visit and compare endpoint between the treatment arms.To investigate the change in the disability rating index at each FU visit and compare endpoint between the treatment arms.To investigate all items assessed in the EQ-5D-5L questionnaire.To investigate the proportion of subjects with full weight bearing at each FU visit and compare this endpoint between the treatment arms.To investigate the change in silver serum levels at each scheduled FU visit and compare endpoint between the treatment arms. The change in silver serum level is defined as the difference between the respective silver level at the respective FU and the silver level at Screening/Enrollment Visit.To investigate the proportion of subjects with Treatment Emergent Adverse Events (TEAEs) during the 12-month FU and compare the rate between treatment arms. A TEAE is considered as any AE observed during the 12-month FU which occurred after the start of the implantation surgery.

**Table 1 Tab1:** List of anticipated adverse device effects

	Incidence proportion
Device-related events	
Implant loosening	
Implant failure (e.g., plate or screw breakage)	3% [15], 5% [16]
Local Argyria^a^	23% [17]
Delayed healing/union	2.5% [18]
Procedure-related events	
Non-union	3.7% [19], 6% [15]
Wound infection	
Superficial infection	17% [15]
Deep infection	19% [20]
Malunion	6% [15], 9.5% [21], 10% [18]

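### Adverse events count from the start of surgery, but the Safety Analysis Set drops patients whose implantation failed, so their events leave the between-arm TEAE comparison

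*Protocol article*

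**What the plan says.** Outcomes {12} lists a between-arm safety comparison: "To investigate the proportion of subjects with Treatment Emergent Adverse Events (TEAEs) during the 12-month FU and compare the rate between treatment arms". It then fixes when counting begins: "A TEAE is considered as any AE observed during the 12-month FU which occurred after the start of the implantation surgery".

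The analysis sets are in section {20c}. On Surgical Failures: "a randomized subject is assigned to the set of surgical failures if the device could not be successfully implanted". On the set named for safety: "Safety Analysis Set includes all treated subjects in the Full Analysis Set who are not Surgical Failures". On its use: "The Safety Analysis Set is used for all primary and secondary analyses and will be analyzed as implanted". The Full Analysis Set keeps every randomised subject, but it is tied only to intention-to-treat analyses and no outcome is named for it.

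Three other places bear on the point:
- Section {11b}, on patients who leave the trial: "The collected data of patients who did not end the trial per protocol will be part of the Safety Analysis Set".
- Section {17a}, on blinding at surgery: "The implanting surgeon and staff involved in the surgery or handling of the investigational device will be unblinded to treatment allocation".
- Section {20a}, on reporting: "For event-based variables (e.g., AEs) the number of events as well as the incidences (i.e., number and percentage of affected subjects) will be provided".

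**The concern.** A safety population should hold everyone in whom the counted harms can occur. Here the clock starts at the beginning of surgery, while membership of the set requires that surgery ended in a successful implantation. A patient whose implantation was begun and then abandoned falls between the two definitions.

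The gap is unlikely to be neutral with respect to harm, because an intraoperative complication may be the reason the implantation was abandoned. The exclusion happens after randomisation, so randomisation no longer protects the comparison. It also arises in an operation whose surgeon knows the allocation.

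What is at stake is the safety summary. The trial has no data safety monitoring board (section {21a}), and the Market approval section says safety must be shown with clinical data. The end-of-study comparison of adverse events should therefore be complete.

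**Working it through.** **Do the definitions conflict?** Two comparisons within the article help.
- The device-related infection outcome in {12} is counted only after successful implantation, which matches the Safety Analysis Set. TEAEs start earlier, so the mismatch is specific to them.
- Incomplete follow-up does not explain the exclusion. Section {11b} keeps the collected data of patients who end the trial early in this same set.

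The set is also analysed by device implanted. A surgical failure has no successfully implanted device, so the rule offers no arm in which to count that patient.

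**How many patients could be affected?** Section {14} gives 192 successfully implanted subjects, a 15% loss to screening and surgical failures together, and a total of 226. The total reproduces: 192 / (1 − 0.15) = 225.9, rounded up to 226. The joint allowance is 226 − 192 = 34, so there are at most 33 surgical failures if even one subject fails screening. The split is not stated. I assume S = 9, 17 or 33 surgical failures, all with surgery started. Then N = 192 + S = 201, 209 or 225, and S/N = 4.5%, 8.1% or 14.7% of randomised subjects leave the comparison.

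**What does that do to the rates?** Let p be the TEAE rate in retained subjects (equal in both arms), q the rate in failures, and f the fraction of an arm that fails. The rate in everyone whose surgery was started is (1 − f)p + fq = p + f(q − p). Exclusion therefore changes:
- each arm's rate by f(q − p);
- the coated-minus-uncoated difference by f_c(q_c − p) − f_u(q_u − p).

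With equal f and q in both arms the second quantity is 0. With q = 1 it becomes (f_c − f_u)(1 − p).

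Assumed splits of 6:3, 11:6 and 22:11, with N/2 per arm, give f_c − f_u = 3/100.5 = 0.0299, 5/104.5 = 0.0478 and 11/112.5 = 0.0978.

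The article gives no TEAE rate, so p is assumed from Table 1. One source cited there reports functional impairment in 66% and pain in 79%. The proportion with any event cannot be below the larger component, so 79% is the better central value for that source. Another source gives 87% for pain. I show all three.

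| | S = 9 | S = 17 | S = 33 |
|---|---|---|---|
| Shift in difference, p = 66% | 1.0 | 1.6 | 3.3 |
| Shift in difference, p = 79% | 0.6 | 1.0 | 2.1 |
| Shift in difference, p = 87% | 0.4 | 0.6 | 1.3 |
| Understatement in each arm, equal split, p = 66% | 1.5 | 2.8 | 5.0 |
| Understatement in each arm, equal split, p = 79% | 0.9 | 1.7 | 3.1 |
| Understatement in each arm, equal split, p = 87% | 0.6 | 1.1 | 1.9 |

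Entries are percentage points with q = 1. The first three rows are (f_c − f_u)(1 − p); for example, 0.0478 × 0.21 = 1.0 points. The last three are (S/N)(1 − p); for example, 0.0813 × 0.21 = 1.7 points. Reversing the split reverses the sign of the shift. If q = p, every entry is 0.

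**How plausible is the split?** If failure risk is the same in both arms, the two-sided binomial probability of a split at least this uneven is 0.51 for 9 failures, 0.33 for 17 and 0.08 for 33. Chance alone can easily produce the two smaller scenarios, but the largest is unlikely without a real difference in failure risk.

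**The case against.** The strongest objection is that the article never explicitly assigns TEAEs to the Safety Analysis Set. That set serves primary and secondary analyses. TEAEs appear in a list of further outcomes, and the abstract names only infection rates and fracture healing as secondary. Mapping outcomes to sets is ordinary work for the statistical analysis plan, and a TEAE table on the Full Analysis Set would not contradict the text. It is true that the link is inferred. But no other set is assigned, the outcome is a safety outcome and the set bears that name. The exclusion itself is stated, so an analysis plan that follows section {20c} would carry it forward.

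The second objection is that nothing need be lost. Surgical Failures is itself a declared analysis set, and section {22} has all adverse events reported. This stands for the individual events, though the article does not say they will be tabulated by arm. It does not restore these patients to the compared proportion.

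The third objection concerns size. The scenarios combine an uneven split with an event in every failure, the devices differ only in their coating, and the article gives no reason for implantation to fail more often in one arm. Table 1 also lists anticipated device effects from other studies, not TEAE rates. All of this stands, and it limits how much weight the point can carry.

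**Conclusion.** The concern holds on the natural reading of sections {12} and {20c}: the set named for safety is narrower than the group in which TEAEs are defined to occur, and the filter can act on the harm being compared.

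The effect is modest and its direction unknown. For 9 to 17 surgical failures and a 79% background rate, the assumed uneven split moves the between-arm difference by about 0.6 to 1.0 points. The near-ceiling case of 33 failures gives 2.1 points but is hard to reach by chance. With equal failure and event rates the difference does not move, although each arm's rate is still too low if failures have more events than other patients. If they have fewer recorded events, for example because they are followed for less time, the rates would instead be too high.

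The number of failures, their split, their event rate and the background rate are all assumptions. Because the TEAE comparison is descriptive and no stated success criterion depends on it, the primary conclusion is not affected. The change is still worth making: it is cheap, and the plan as written gives a poorer safety comparison.

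**What to change.** In section {20c}, assign the TEAE comparison to all randomised subjects in whom the implantation surgery was started, grouped by the device received or, where implantation failed, the device attempted. Report adverse events in Surgical Failures separately by arm. Keep the successfully implanted set as a supportive analysis for this outcome.

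This changes one set assignment for one outcome and leaves the primary analysis alone. Table 2 already schedules adverse event reporting at the implantation visit, so events at a failed operation fall within planned collection. There are two costs. The TEAE rates may look slightly less favourable. The article also does not establish that surgical failures are followed for 12 months, so their data should be used as collected, with length of follow-up shown.

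### The primary non-inferiority test is assigned to an as-implanted set that drops randomised surgical failures, and no primary or secondary analysis is assigned to the as-randomised set

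*Protocol article*

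**What the plan says.** Section {20c} of the protocol article defines four analysis sets.

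- **Surgical failures:** "a randomized subject is assigned to the set of surgical failures if the device could not be successfully implanted". Membership is therefore settled after randomisation.
- **Full Analysis Set:** "Full Analysis Set employs the intent-to-treat principle and includes all subjects randomized", analysed by randomised arm. Its stated role is: "The Full Analysis Set population is used for all intent-to-treat-based analyses". No such analysis is named.
- **Safety Analysis Set:** "Safety Analysis Set includes all treated subjects in the Full Analysis Set who are not Surgical Failures". Its role is: "The Safety Analysis Set is used for all primary and secondary analyses and will be analyzed as implanted".
- **Per Protocol set:** drawn from the Full Analysis Set and used for key analyses only if it holds fewer than 90% of that set.

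Section {20b}, on additional analyses, adds: "No subgroup or other additional analyses for this clinical trial is planned".

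Under {16b} the unblinded surgeon randomises through the eCRF on the day of implantation. Under {17a}: "The implanting surgeon and staff involved in the surgery or handling of the investigational device will be unblinded to treatment allocation". The reason given there is that the coating can be seen.

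The sample size section {14} counts successfully implanted subjects (96 per arm, 192 in all). It covers screening failures and surgical failures together with a 15% allowance.

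**The concern.** The primary hypothesis in {20a} compares the proportions of subjects with at least one predefined AADE. It decides the trial's only stated confirmatory claim. Two rules in {20c} separate that comparison from the randomisation: subjects leave after allocation if implantation does not succeed, and the remainder are grouped by the plate they received. Both are settled in theatre, by or in the presence of people who know the allocation.

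A failed or switched implantation may go with a difficult fracture or poor soft tissue, and so with a higher AADE risk. Surgical failures also remain at risk of events that Table 1 lists as procedure-related, such as haematoma, neurovascular lesion and compartment syndrome. If more high-risk subjects leave the coated arm than the uncoated arm, the observed difference shrinks and non-inferiority becomes easier to declare. As the article stands, no named analysis of the primary endpoint would show whether this had happened.

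**Working it through.** **1. The plan's own figure.** 192/(1 − 0.15) = 225.9, rounded up to 226; 96/0.85 = 112.9, rounded up to 113 per arm. The total is reproduced. Surgical failures are thus an expected part of attrition, but their share of the 15% is not given.

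**2. The AADE rate behind 96 per arm.** No rate is stated. With no true difference, margin 0.10, one-sided 5% and 80% power, n = 2p(1 − p)(1.645 + 0.842)²/0.10². Setting n = 96 gives p(1 − p) = 0.0776, so p is about 8.5% or, equally, about 91.5%. Table 1 lists pain at 25% to 87% and functional impairment at 52% to 66%, so the low root cannot be taken for granted. A range is needed.

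**3. Effect of the exclusion on the type I error (illustrative).** Assumptions: 113 randomised per arm; a true difference of exactly +0.10 among all randomised, so that the error should be 5%; a fraction f of the coated arm excluded and none of the control arm; no crossover. If the excluded subjects have event risk q, the coated rate left in the Safety Set is

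p₁* = (p₁ − f·q)/(1 − f), with p₁ = p₀ + 0.10.

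The probability of declaring non-inferiority (upper 90% bound below 0.10) is, by normal approximation,

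Φ[(0.10 − (p₁* − p₀))/SE − 1.645], with SE² = p₀(1 − p₀)/113 + p₁*(1 − p₁*)/(113(1 − f)).

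*Same risk (q = p₁):* p₁* = p₁, and the error stays at 5.0% for every f.

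*Worst case (q = 1), f = 5%, p₀ = 8.5%:* p₁* = (0.185 − 0.05)/0.95 = 0.142, difference 0.057, SE = 0.0427, and Φ(1.004 − 1.645) = 26.1%.

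False non-inferiority probability in the worst case:

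| Control rate | f = 2% | f = 5% | f = 10% |
|---|---|---|---|
| 8.5% | 10.2% | 26.1% | 74.9% |
| 50% | 6.4% | 9.2% | 16.1% |
| 81.5% | 5.4% | 6.1% | 7.5% |

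The last row is the high-rate counterpart of the first: the coated rate at the null boundary is then 91.5%.

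**4. Power if all randomised subjects are analysed.** With 113 per arm, no missing outcomes and a rate of 8.5% or 91.5%, power is 85.3%, against 79.9% at 96 per arm. If surgical failures, equal in both arms, were themselves counted as events, a base rate of 8.5% becomes f + (1 − f) × 0.085. Power at 113 per arm is then 79.5%, 72.1% and 62.8% for f = 2%, 5% and 10%. At a base rate of 91.5% it is 86% to 88%. The 226 are described as screened subjects, so fewer than 113 per arm may be randomised, and these powers are upper limits.

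**The case against.** The strongest defence is that AADEs are device effects, that a set of implanted subjects is customary for such outcomes, and that the choice is prespecified and matches a sample size built on successful implantations. Nothing in the document points to unequal failure: {6b} and the oversight section {5d} say that the plates differ only in the coating. This stands as a reason to keep an as-implanted analysis. It does not make that analysis sufficient for the confirmatory test, because the composite also contains procedure-related outcomes for which failed implantations remain at risk.

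An as-randomised analysis is not automatically the safer one either. Crossovers pull the contrast towards zero, which favours non-inferiority. That also stands, and it argues for requiring both.

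Four stronger readings may tempt a reader, and the text does not carry them.

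- *That the Full Analysis Set is never used.* It is reserved for intent-to-treat analyses, is the base of the Safety and Per Protocol sets, and is the denominator of the 90% trigger. The analysis plan, which is not shown, could name such an analysis. Section {20b} concerns additional analyses such as subgroups and is weak evidence that none will be run.
- *That the surgeon classifies surgical failures.* The article does not say who does. It is a reasonable inference from {16b} and {17a}, no more.
- *That exclusion hides the very inferiority under test.* Failed implantation is not a listed AADE. Counting it as an event, with 5% against 2% failures assumed, gives a hidden difference of 0.03 × (1 − p): 2.7 points at p = 8.5% but only 0.26 points at p = 91.5%. Either figure describes a different endpoint from the protocol's.
- *That the follow-up data certainly exist.* Section {18b} says that patients who deviate from the plan are followed like the others. It does not mention surgical failures.

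**Conclusion.** The point holds as a fault in a stated rule, not as missing detail. The confirmatory non-inferiority test is placed on a set defined by events after randomisation and grouped by implant received, and no primary or secondary analysis is assigned to the set that preserves randomisation. The comparison is exposed to selection; the document does not show that it is biased.

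The size cannot be derived, because the article gives no surgical-failure rate, crossover rate or AADE rate. With no failures and no crossovers the two sets coincide. With failures whose AADE risk equals that of the rest, the error stays at 5%. The figures of about 26%, 9% and 6% at control rates of 8.5%, 50% and 81.5% rest on 5% failures in the coated arm alone, all of them with an AADE. They are a worst case for that failure rate, not a forecast. The change should still be made before database lock, because the rule governs the primary conclusion and is cheap to correct.

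**What to change.** Change {20c} so that the AADE comparison is run on the Full Analysis Set as randomised, either as the primary analysis or as co-primary with the Safety Set, with non-inferiority required in both. Keep surgical failures in and count them by their observed AADEs. Treat failure-as-event as a sensitivity analysis only: as the primary rule it would change the endpoint and could lower power to about 72% (5% failures in both arms, base rate 8.5%, 113 per arm). State who classifies a surgical failure. Keep the as-implanted Safety Set for the tables of treatment-emergent adverse events and silver levels and, where it is not co-primary, as a supportive analysis of AADEs.

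The cost is a wording change and one extra run of the primary table. It must also be confirmed that surgical failures are followed for AADEs to 12 months. As-randomised analysis of crossovers dilutes the contrast, which is why the as-implanted analysis is retained.
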